## Abstract

**Background:**

Depression and Alcohol Use Disorders (AUDs) are two leading causes of disability worldwide and are associated with significant treatment challenges requiring new, innovative, cost-effective and technologically-based therapies including the use of supportive text messages.

**Objective:**

To determine the feasibility and effectiveness of supportive text messages in long-term follow-up to reduce mood symptoms and problem drinking in patients with Depression or AUD respectively and to explore the usefulness of self-reports of health services utilization as an outcomes measure.

**Methods:**

This will be a longitudinal, prospective, parallel-design, two-arm, placebo-controlled single-rater-blinded randomized clinical trial with a recruitment period of 6 months and an observation period of 12 months for each participant, with two strata based on primary diagnosis of Major Depressive Disorder or AUD. The sample size will be 120, with about 60 patients randomized from each primary diagnostic grouping. Patients in all intervention groups will receive twice-daily supportive SMS text messages for 3 months and then daily supportive text messages for the next three months. Patients will also receive a phone call every two weeks from the research assistant assigning treatment allocation to confirm that they are still receiving the text messages and to thank them for taking part in the study. Patients in the control group will receive no text messages but will also receive a phone call from the same research assistant every two weeks to thank them for taking part in the study.

**Results:**

The study starts in April 2015 and ends in September 2016. It is envisaged that both qualitative and quantitative primary and secondary outcomes, including patient perceptions of the intervention, will shed light on the feasibility of using automated supportive text message interventions in long term for patients with Depression and AUD. This will inform a full-scale clinical trial.

**Conclusions:**

The paradigm for behavior change using text messages as a patient-direct intervention is consistent with a cognitive behavior therapy approach and addictions counselling principles. Given the automaticity of the messages, we anticipate that if the intervention proves successful, it will represent a low cost strategy that will be readily available and can bring relief to patients in hard-to-reach areas with limited access to psychological therapies.

**Trial Registration:**

ClinicalTrials.gov: NCT02327858; https://clinicaltrials.gov/ct2/show/NCT02327858 (Archived by WebCite at https://clinicaltrials.gov/ct2/show/NCT02327858).

## Introduction

### Background

Depression and Alcohol Use Disorders (AUDs) are leading causes of disability worldwide, associated with significant treatment challenges especially when they occur concurrently [1, 2]. Concurrent challenges include: higher rates of lifetime drug dependence [3]; worse outcomes among those entering treatment for alcohol and drug misuse [4]; higher relapse following AUD treatment among adolescents [5] and adults [6]; greater severity of suicidality in adults [7], and higher likelihood of suicide attempts [8-10] and completed suicides [11]. Given this acute disease burden, we propose a treatment strategy that takes advantage of mobile phone technology to support patients in an efficient, innovative and cost-effective manner. The ultimate aim is to restore health while reducing the combined impact of these disorders on patients, caregivers, their communities and Alberta’s provincial health care provider, Alberta Health Services (AHS) [12].

In a pilot trial in Ireland, participants with concurrent depression and AUD who completed an inpatient dual diagnosis treatment program were randomized to receive twice-daily supportive text messages or a biweekly “thank you” text message for three months. Supportive text messaging improved Beck Depression Inventory (BDI) scores compared with those who received standard care. There was also a trend towards increased Cumulative Abstinence Duration (CAD) in the supportive text message group [13]. Furthermore, the majority of patients who received the supportive text messages expressed satisfaction with the support offered through the technology [14]. The pilot trial in Ireland did not explore the effects of supportive text messages on the individual disorders when they occur alone, although it would be reasonable to assume that they would benefit equally. A recent study in JAMA Psychiatry [15] randomly assigned patients leaving residential treatment for AUDs to either use of a smartphone application to support recovery in addition to standard treatment or treatment as usual. For the 8 months of the intervention and 4 months of follow-up, patients in the smartphone application support group reported significantly fewer risky drinking days than did patients in the control group. In a review of efficacy of use of text messaging as a clinical and healthy behavior intervention, Wei et al (2011) found that among 16 randomized controlled trials, 10 reported significant improvement with interventions and 6 reported differences suggesting positive trends [16]. More recently, in a meta-analysis of the results of text message interventions among 14 studies, the pooled effect size was 0.25, 95% CI (0.13-0.38), indicating that in general, text interventions have a positive effect on reducing substance use behaviors [17].

### Overall Aims

To conduct a randomized controlled pilot trial to determine the feasibility, acceptability and effectiveness of supportive text messages in long-term care to reduce mood symptoms and problem drinking in patients with Depression or AUD respectively.

### Specific Objectives

1. To compare mean changes in BDI scores from baseline for patients with Depression receiving standard care with supportive text messages to those receiving standard care without supportive text messages.

2. To compare the CAD from baseline for patients with AUD receiving standard care with supportive text messages to those receiving standard care without supportive text messages.

### Hypotheses

Supportive text messages will:

1. Lead to a 30% better mean reduction in BDI scores at 6 months from baseline in the intervention group compared to the control group.

2. Increase the mean Cumulative Abstinence Duration (CAD) for patients with AUD in the intervention group from baseline by at least 30% over and above the mean CAD for patients in the control group from baseline.

## Methods

### Study Design and Setting

This will be a longitudinal, prospective, parallel-design, two arm, placebo-controlled single-rater-blinded randomized clinical trial with a recruitment period of 6 months and an observation period of 12 months for each participant with two strata based on primary diagnosis of Major Depressive Disorder or AUD. Patients with AUD will be recruited from those completing the Northern Addiction Residential Treatment program located in Grande Prairie while patients with Depression will be recruited from those assessed for wait listing onto the Cognitive Behavior Therapy (CBT) program run by the Adult Mental Health Team in Fort McMurray. The study has received ethical clearance from the Health Ethics Research Board of the University of Alberta and operational approval from the AHS. All participants will provide informed written consent prior to randomization. The study has been registered with clinicaltrials.gov (NCT02327858) and will be executed according to the timelines specified in the Gantt chart in Table 1.

**Table 1 table1:** Gantt chart for supportive text message project.

		Year 1				Year 2				Year 3			
		Start Date-End Date				Start Date-End Date				Start Date-End Date			
Milestones		Q1	Q2	Q3	Q4	Q1	Q2	Q3	Q4	Q1	Q2	Q3	Q4
**Milestone 1: Recruiting and training of research associates**													
	1.1 Advertising and assembling of research associates	X											
	1.2 Training of research associates and the trainee in psychiatry	X											
	1.3 Writing up a bank supportive text messages in collaboration with service users and CBT and addiction counselors	X											

**Milestone 3: Follow-up assessment of study participants and collection of administrative data**													
	3.1 Follow-up assessments of individual study participants (Excluding survey on the usefulness of the supportive text messages)			X	X	X	X	X					
	3.2 Follow-up survey of participants in the intervention group on the usefulness of supportive text messages				X	X							
	3.3 Collection of administrative data related to cost of health services utilization						X	X					
**Milestone 4: Data compilation, analysis and preparation of reports, publications and presentations**													
	4.1 Data compilation		X	X	X	X	X	X					
	4.2 Data Analysis		X	X	X	X	X	X	X				
	4.3 Preparation of reports, publications and presentations								X	X			

### Recruitment

All patients completing the Northern Addiction Residential Treatment program located in Grande Prairie and those assessed for waitlisting onto the Cognitive Behavior Therapy program run by the Adult Mental Health Team in Fort McMurray who fulfill the inclusion criteria below will be invited to participate. This will minimize source of referral as a confounding factor. Information leaflets will be provided and those consenting will be recruited. The Structured Clinical Interview for DSM-5 Disorders (SCID) will be used to screen and confirm the diagnosis of all study participants prior to inclusion in the study.

### Inclusion Criteria

Persons aged 18 years and over who are able to provide informed consent will be eligible if they have been assessed and waitlisted for the CBT program in Fort McMurray and fulfill the DSM-5 diagnostic criteria for Major Depressive Disorder or who have completed the residential addiction treatment program located at the Northern Addiction Treatment Centre, fulfill the DSM-5 diagnostic criteria for AUD and are in the stage of change and are committed and motivated to give up alcohol. Participants must be familiar with or willing to learn how to receive text messages and be available for long-term intervention. Mobile phone handsets and top-up call credit of up to 10 dollars monthly will be provided to those who satisfy the inclusion criteria but do not have mobile phones*.*

### Exclusion Criteria

Patients will be ineligible if they do not meet the above inclusion criteria, if they are patients with Schizophrenia, Schizoaffective Disorder, Bipolar Disorder and other psychotic disorders, or residing outside of regular cell phone connection areas.

### Baseline Assessment

All study participants will undergo baseline assessments during recruitment to collect demographic and clinical data. For those with AUD, the time-line follow back (TLFB) [18] will be used to record the quantity of alcohol consumed and number of drinking days during the 90 days preceding the admission to the recovery centre. We will also record any history of alcohol-related pathology. For those with Depression, the BDI will be used to record baseline depression symptom scores. Other clinical measures will include the Obsessive Compulsive Drinking Scale (OCDS)[19] and the Alcohol Abstinence Self-Efficacy Scale (AASES) [20] that evaluates both temptation to drink and confidence to abstain across 20 items representing cues in the four subscale areas of Negative Affect, Social, Physical, and Withdrawal/Urges.

Functional outcome will be assessed by measuring the Health Related Quality of Life (HRQOL). The HRQOL will be measured by the Canadian version of the EQ-5D-5L instrument from all patients. The EQ-5D-5L consists of two components: a five dimensional descriptive system including mobility, self-care, usual activities, pain or discomfort and anxiety or depression with five levels in each of them, and a Visual Analogy Scale (VAS) where respondents value ‘their own health today’ on a scale from 0 (worst imaginable health state) to 100 (best imaginable health state). It is cognitively simple, taking only a few minutes to complete and it can also be used to calculate single index values for economic and population health studies.

### Randomization and Blinding

Randomization will be stratified by primary diagnoses (Depression or AUD) using permuted blocks to ensure balance (1:1) between treatment and control groups within each condition under study. The randomization codes will be transmitted by an independent statistician via text message directly to the researcher. This will commence immediately after the participant has signed the consent form. A dedicated, password-protected phone line with a secure online backup will be used to transmit these messages.

The research assistant who sends the text messages will not be involved in the outcome assessments except to contact those receiving the supportive text messages for feedback on the benefits of the text messages. Participants cannot be blinded and treatment allocation will be made explicit to them. Outcome assessors will be blinded to treatment group allocation. To ensure this, treatment allocation will be concealed from the outcome assessor by blocking access to the database, which contains the randomization code, and all participants in the study will be asked not to reveal their treatment allocation to their assessor. Outside the assessments, outcome assessors will not participate in discussions with the participants in study forums. To test the success of blinding we will ask the assessor to guess the allocation group for each participant at 3, 6, 9 and 12-month follow-ups. Moreover, these assessors will not be involved in data analysis. After data collection is complete all data will undergo a blind review for the purposes of finalizing the planned analysis. Every effort will be taken to avoid incomplete data and methods of dealing with unanticipated missing data will be determined during the blind review of the data.

### Intervention

Patients in all intervention groups will receive twice-daily supportive SMS text messages for 3 months and then daily supportive text messages for the next three months. The messages will be tailored towards improving mood, compliance with medication or targeting abstinence from alcohol in accordance with the primary aims of our study. The majority of the text messages will reflect lessons patients usually learn during CBT and addiction counseling sessions in the two recruitment sites and sent at specified times by a centralized computer program which will be set up and monitored by a research assistant. Sample text messages are outlined below.

If you keep on going, maintaining your hope and belief that something good will happen, it generally does. One day at a time.Ask for help. You have lent a hand to others in need in the past. There is probably someone in your life that would be genuinely honored to help you now.Give yourself the time you need to recover, do not try to race ahead to where you think you should be, remember that time is a great healer.Think of your recovery as an opportunity to find new solutions in your life. Remember that the past is gone and what you do next is what really matters.

To safeguard patient confidentiality no identifiable patient information will be transmitted via text messages. Patients will also receive a phone call every two weeks from the research assistant assigning treatment allocation to confirm that they are still receiving the text messages and to thank them for taking part in the study. Patients in the control group will receive no text messages but will also receive a phone call from the same research assistant every two weeks to thank them for taking part in the study. The aim of this will be to help increase the retention rate for the study.

### Sample Size

Consistent with the idea that this is a pilot study, the research will use the data that can be elicited from participants who can be enrolled within the existing resources [21]. The study will therefore be limited to a sample size of 120, with about 60 patients randomized from each primary diagnostic grouping.

### Follow-up Assessments

At 3, 6, 9 and 12 months, a blinded researcher (a research psychologist) will contact all patients over the phone and assist them in completing a range of assessment tools relating to the primary and secondary outcome measures. The research assistant who randomized the patients will contact patients in the intervention group by telephone at 6 months to get their views on the usefulness of the supportive text messages. All patients will be similarly contacted regarding their satisfaction with their treatment using a semi-structured questionnaire. At 12 months, data related to each patient’s utilization of health services and their associated costs will be compiled from AHS administrative records by the blinded research associate.

### Primary Outcome Measure

1. Mean changes in the BDI scores from baseline for those with a primary diagnosis of Depression

2. CAD from baseline (since discharge from the Residential Addiction treatment program) for those with primary AUD.

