### Secondary Outcome Measures for Patients With Primary AUD

1. Mean units of alcohol per drinking days for participants with AUD at 3, 6, 9 and 12 months, computed from self-reports.

2. Mean number of days to the first drink for participants with AUD, computed from self-reports.

3. Number of hazardous drinking days (drinking in excess of the safe limits) from baseline for participants with AUD at 3, 6, 9 and 12 months, computed from self-reports.

4. Mean changes in the scores on the OCDS from baseline for participants with AUD at 3, 6, 9 and 12 months.

5. Mean changes in the scores on the Alcohol Abstinence Self-Efficacy Scale from baseline for participants with AUD at 3, 6, 9 and 12 months

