### Secondary Outcome Measures for Patients With Either Primary AUD or Primary Depression

1. Improved EQ-5D-5L scores from baseline. Health related Quality of Life will be measured in all groups at baseline, 3, 6, 9 and 12 months using the EQ-5D-5L (Canadian version).

2. Quantitative and qualitative data will be gathered from all participants in the intervention group using the semi-structured questionnaire in Multimedia Appendix 1 to assess their perceptions about how helpful or unhelpful the supportive text messages were to the course of their recovery.

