### Statistical Methods

Since it is unlikely that this pilot study will be powered to detect sufficiently small clinically relevant differences, the primary purpose of the statistical analysis for this pilot study will be a thorough descriptive analysis of the data, with a view to understanding the amount and mechanism for any missing data. In particular one of the goals will be to determine the feasibility of long-term impact of supportive text message treatment and follow up in this population. An analysis of missing data may help to determine how to improve follow-up and retention of patients in the full study.

A secondary goal will be to examine the patterns of the longitudinal data, which will guide the planned analysis for a full study (e.g. using a Generalized Estimating Equation [GEE] approach or a generalized linear mixed models [GLMM] approach). In particular for each outcome measure we will look at the correlation between successive time points. Analyses will be done within each diagnostic group separately.

A final goal will be to produce summary statistics for the longitudinal data, which will provide estimates for future sample size calculations. A clinically meaningful difference has already been determined as in the stated hypotheses for the full study. From this pilot study we will be able to estimate the variability in the estimates that we would expect to see, which will help to guide the sample size estimation.

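### The BDI and secondary scale comparisons are worded as differences in mean change from baseline; state that they use the baseline score as a covariate, and report the matching planning values

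*Protocol article*

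**What the plan says.** All references are to the protocol article.

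- **Specific Objectives, item 1** gives the between-arm comparison for the Depression stratum: "To compare mean changes in BDI scores from baseline for patients with Depression receiving standard care with supportive text messages", set against standard care without the messages.
- **Primary Outcome Measure, item 1** repeats it as the outcome: "Mean changes in the BDI scores from baseline for those with a primary diagnosis of Depression". Item 2, for alcohol use disorder (AUD), is of a different kind: "CAD from baseline (since discharge from the Residential Addiction treatment program) for those with primary AUD".
- **Secondary outcomes** follow the change wording: "Mean changes in the scores on the OCDS from baseline for participants with AUD at 3, 6, 9 and 12 months", "Mean changes in the scores on the Alcohol Abstinence Self-Efficacy Scale from baseline for participants with AUD" and, for both strata, "Improved EQ-5D-5L scores from baseline".
- **Baseline Assessment** has the BDI, OCDS, AASES and EQ-5D-5L recorded at entry.
- **Randomization and Blinding** stratifies by primary diagnosis only, so baseline severity within a stratum is left to chance. The planned analysis is to be finalised at a blind review once data collection is complete.
- **Statistical Methods** describes a mainly descriptive analysis, done separately within each diagnosis. It will examine correlations between successive time points, and it mentions GEE or GLMM as possible models for the full study. It also sets this aim: "A final goal will be to produce summary statistics for the longitudinal data, which will provide estimates for future sample size calculations". It does not say which SD will serve that aim, and it mentions no baseline covariate.

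**The concern.** If the objective is carried out as worded, each arm's mean change is computed and the two are subtracted. That fixes the weight on the baseline score at exactly 1. Unless the true regression slope of follow-up on baseline is also 1, this has two costs.

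First, the estimate has more variance than one that lets the data set the slope. Second, it over-corrects when the arms differ at baseline by chance: the arm that starts worse tends to show the larger improvement through regression to the mean, whatever the treatment does. At about 30 per arm such imbalance is common.

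The pilot's between-arm estimates are descriptive, so no confirmatory conclusion is at risk. What is at stake is the width and stability of those estimates, and whether the pilot yields the quantities needed to size a full trial that adjusts for baseline.

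**Working it through.** **Inputs from the article.** The total is 120, with about 60 per diagnosis and 1:1 allocation, so 60 / 2 = about 30 per arm per stratum. The 120 is set by resources and has no power calculation behind it, so there is no planning figure to reproduce.

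**Assumed inputs.** The article gives no SD and no correlation. Let rho be the correlation between baseline and follow-up, and measure everything in units of the follow-up SD.

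**Step 1: equal SDs at baseline and follow-up.**
Var(change) = 2(1 − rho). Var(baseline-adjusted residual) = 1 − rho². The ratio adjusted/change is (1 + rho)/2. The 95% half-width at 30 per arm is 1.96 × SD × √(2/30).

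| rho | SD of change | Residual SD | Variance ratio | Half-width, change | Half-width, adjusted |
|---|---|---|---|---|---|
| 0.3 | 1.183 | 0.954 | 0.65 | 0.60 | 0.48 |
| 0.5 | 1.000 | 0.866 | 0.75 | 0.51 | 0.44 |
| 0.7 | 0.775 | 0.714 | 0.85 | 0.39 | 0.36 |
| 0.9 | 0.447 | 0.436 | 0.95 | 0.23 | 0.22 |

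**Step 2: cost of estimating the slope at this size.** A simulation at 30 per arm (10,000 replicates, normal data) gave variance ratios of 0.68, 0.77 and 0.87 at rho 0.3, 0.5 and 0.7. A change-score analysis would need about 30/0.68 = 44, 30/0.77 = 39 or 30/0.87 = 34 patients per arm to match the adjusted analysis with 30.

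**Step 3: chance imbalance.** The standard error of the baseline difference between arms is √(2/30) = 0.26 SD. A difference beyond 0.25 SD in either direction therefore has a probability of about one in three for any one scale in a stratum. Given a baseline difference D, the change-score contrast is shifted by (1 − rho) × D. For D = 0.25 SD this is 0.175, 0.125 or 0.075 SD at rho 0.3, 0.5 or 0.7.

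**Step 4: sensitivity to a narrower baseline spread.** If the baseline SD is k times the follow-up SD, the ratio is (1 − rho²)/(1 + k² − 2k·rho). The denominator exceeds the numerator by (k − rho)², so in large samples the ratio never exceeds 1. Taking k = 0.7 as an illustration:

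- rho 0.3: 0.91/1.07 = 0.85
- rho 0.5: 0.75/0.79 = 0.95
- rho 0.7: 0.51/0.51 = 1.00

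In the last case the true slope is 1 and adjustment gains nothing.

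**Step 5: what this means for planning.** If the full trial adjusts for baseline but is sized on the SD of change, the excess is 1/ratio − 1. With equal SDs that is 54%, 33%, 18% and 5% at rho 0.3, 0.5, 0.7 and 0.9. With k = 0.7 it is about 18%, 5% and 0% at rho 0.3, 0.5 and 0.7. If the full trial compares change scores, the SD of change is the right input and there is no excess.

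**The case against.** The strongest reply is that the article defines variables, not a model. A change score can be analysed with its baseline value as a covariate, and the treatment estimate is then the same as from ANCOVA on the follow-up score. The choice of model is open until the blind review, and a separate analysis plan may name the covariates. All of this is correct. A reader might infer that the article commits the trial to an unadjusted test, and it does not. What remains is that the comparison is stated as one of mean changes, and nothing in the article points towards adjustment.

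Two other strong readings are tempting and also fail:

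- **That both primary outcomes are affected.** CAD is a duration counted from discharge. It is not a change score and has no like-for-like baseline value, because the baseline drinking record covers the 90 days before admission. The formulas above do not apply to it. Adjusting CAD for earlier drinking would be an optional refinement.
- **That an inflated SD will be passed to the full trial.** Statistical Methods names no SD. Summary statistics together with correlations could supply a residual SD. The gap is narrower: correlations between successive time points may cover adjacent visits only and so omit baseline to 6 months, which is the pair that the BDI hypothesis needs.

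It is also fair to say that the size of the gain is uncertain. Depression patients must meet diagnostic criteria at entry, so a narrower baseline spread is plausible, and Step 4 shows how far that could reduce the gain. In a pilot whose analysis is mainly descriptive, the consequence is modest.

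**Conclusion.** The point holds as a minor one, for the BDI in the Depression stratum and for the OCDS, AASES and EQ-5D-5L. As worded, these comparisons are generally less precise than baseline-adjusted ones and are exposed to chance baseline imbalance at about 30 per arm.

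Under equal SDs and rho between 0.3 and 0.7, adjustment lowers the variance by about 13% to 32% at this sample size (ratios 0.87 to 0.68). Those assumptions are not from the article. The gain falls towards nothing as rho rises towards 1, or where the slope of follow-up on baseline is close to 1. The actual loss therefore cannot be quantified from the article.

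On planning, the supported statement is conditional: the SD of change would oversize the full trial only if that trial adjusts for baseline. The article does not say which SD it will use, and the correlations it plans may not include the one needed to convert between them.

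**What to change.** 1. In Statistical Methods, state that between-arm estimates for BDI, OCDS, AASES and EQ-5D-5L come from ANCOVA, or from a mixed model over 3, 6, 9 and 12 months, with the baseline score as covariate. Keep mean change from baseline by arm as a descriptive summary.
2. In the paragraph on future sample size, list the planning values to be reported for each scale: the follow-up SD, the baseline-to-6-month correlation and the baseline-adjusted residual SD. Extend the planned correlations beyond successive time points so that this pair is included.
3. Say that the SD used to size the full trial will match the analysis chosen for that trial.

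The cost is wording only. Every baseline score is already collected, and no visit, instrument or patient is added. The change can be made before, or at the latest during, the blind review that finalises the analysis.
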